### Aims and hypotheses

This study will conduct a longitudinal, single-blinded, randomized controlled trial to verify the clinical effects of different protocols of rTMS therapy on functional recovery of chronic subcortical stroke patients with severe hemiplegic upper limb. To the best of our knowledge, this is the first study to compare the effects of low-frequency rTMS on cM1 and high-frequency rTMS on cPMd. We expect that the findings will provide vital information about the optimal rTMS strategy. Multimodal fMRI scanning and electrophysiological measurements will be performed longitudinally to elucidate the underlying neural mechanism of brain reorganization after different parameters of rTMS therapy. We hypothesize that high-frequency rTMS on cPMd might be the optimal protocol for motor functional recovery in chronic subcortical stroke patients with severe hemiplegia. This clinical effect may be attributed to the specific remodeling patterns of structural, functional, or effective connectivity of homologous or allogeneic cortexes within or between hemispheres through multimodal neural imaging analysis. Furthermore, joint analysis of the clinical and neuroimaging results might identify the cut-off of structural reserve that determines the application of high/low frequency rTMS on contralesional hemisphere to achieve maximum functional recovery of the paretic upper limb.

## Methods/design

### Study design

The study will be conducted at Huashan Hospital, Fudan University and The Third Rehabilitation Hospital, Shanghai. Signed informed consent will be obtained from all participants prior to the study. Briefly, chronic (onset time > 3 months) subcortical stroke patients with severe hemiplegia will receive conventional rehabilitation treatment and three different protocols of rTMS intervention: low-frequency rTMS of cM1, high-frequency rTMS of cPMd, and sham stimulation. Next, multimodal fMRI scanning (DTI, rs-fMRI, and tb-fMRI), functional assessments, and electrophysiological assessments will be performed before intervention (T0), 3 weeks after intervention (T1), and 4 weeks after the end of treatment (T2), respectively. Figure 1 shows the flow-diagram of the study design.

**Fig. 1 Fig1:**
[figure not shown]
Flow chart showing the study design. CRT, conventional rehabilitation training; cM1, contralesional primary motor cortex; cPMd, contralesional dorsal premotor cortex; LF, low frequency; HF, high frequency; rTMS, repeated transcranial magnetic stimulation

Patients will be recruited from Huashan Hospital Fudan University and the Third Rehabilitation Hospital of Shanghai. The legal rights and interests of them will not be violated during the study. For the intervention, subjects’ privacy will be fully respected and their personal information will be kept strictly confidential.

### Inclusion and exclusion criteria

A total of 60 eligible patients will be recruited from Huashan Hospital, Fudan University. The inclusion and exclusion criteria are listed in Table 1.

**Table 1 Tab1:** Inclusion and exclusion criteria

Criteria	Description
Inclusion criteria	➤ First-ever stroke ➤ Subcortical stroke diagnosed by head CT or MRI ➤ Clear consciousness and stable vital signs ➤ 18–80 years old ➤ 3–12 months since stroke onset ➤ Unilateral hemiplegia, Brunnstrom stage of affected hand ≤ IV ➤ Right-handed
Exclusion criteria	➤ Severe speech, attention, hearing, vision, sensation, intelligence, mental, or cognitive impairments (MMSE score < 27) ➤ Severe spasticity (Modified Ashworth Spasticity Scale > 2) or pain (Ten-point Visual Analog Scale > 4) of the affected side ➤ Bone, joint, and muscle diseases, other serious nervous system diseases, malignant tumors, and serious heart, lung, liver, and kidney damage ➤ Still enrolled in any rehabilitation or drug studies ➤ Metal implant, magnetic sheet, or cardiac pacemaker ➤ Alcohol or drug addiction ➤ Epilepsy

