## Background

Hemiplegia is one of the most common functional defects after stroke. Although stroke patients can recover spontaneously, most patients in the chronic phase will still suffer from upper limb dysfunction, especially hand dysfunction. It seriously affects the patients’ abilities of daily living, and imposes a heavy burden on their families and the society [1].

Transcranial magnetic stimulation (TMS), one of the non-invasive brain stimulation (NIBS) techniques, have been widely used in research and clinical treatment to promote the recovery of motor function in stroke patients due to its safety, noninvasiveness, and painlessness [2, 3]. Repeated TMS (rTMS) is a commonly used stimulation mode developed on the basis of TMS. High frequency rTMS (≥1 Hz) has an excitatory effect on cortex neurons, whereas low frequency rTMS (< 1 Hz) inhibits the activity of cortex neurons [4–6]. In recent years, rTMS has shown a great potential in stroke rehabilitation, with many studies reporting that it can improve the motor function of stroke patients with hemiplegia [7–10]. However, there are also studies reported contrasting results that rTMS does not confer additional benefits in the treatment of hemiplegia [11–14], with some studies even reporting mild functional regression after rTMS treatment [15, 16]. Moreover, recent reviews on the clinical efficacy of rTMS in the treatment of stroke hemiplegia did not reach a consistent conclusion, especially in patients with severe hemiplegia or at chronic stage [13, 17–20]. According to the Clinical Application Guidelines for rTMS (2018) [21], level A evidence supports the use of low-frequency rTMS on contralesional M1, and level B evidence suggests application of high-frequency rTMS on ipsilateral M1 in patients with sub-acute stroke. However, there is no clear recommendation for rTMS stimulation parameters in patients with chronic stroke. Therefore, this calls for high quality evidence that will be used to develop an optimal rTMS protocol for chronic stroke patients with severe hemiplegia.

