### Randomization and grouping

The 60 eligible stroke patients will be randomly assigned to three groups with 20 patients in each group: low-frequency rTMS of cM1 (cM1-LF) group, high-frequency rTMS of cPMd (cPMd-HF) group, and sham-stimulation control (CON) group. The random sequence will be created using STATA 12.0 software (StataCorp, Texas, USA) by a professional third-party statistician from Fudan University. The randomization list will only be known by this research coordinator and will be concealed from other study personnel. However, the research coordinator will not participate in recruitment, subsequent intervention and assessment, and final data analysis. In addition, 20 healthy people will be recruited into the healthy control (HC) group. The HC group will be matched with stroke groups in terms of age, gender, and education.

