#### Group-level analysis

All statistical analyses will be performed using SPSS software (SPSS 25.0, SPSS Inc., Chicago, Illinois). The intention-to-treat principle will be used for the analysis of functional and electrophysiological data. One-way analysis of variance (ANOVA) will be used to compare the demographic characteristics and baseline assessment (T0) of all outcomes among groups. To compare the treatment effects of different rTMS protocol, a two-way mixed design ANOVA with between-subject factor “Group” and within-subject factor “Time” will be performed for the clinical and electrophysiological changes. Moreover, Bonferroni correction will be employed for post hoc multiple comparisons. *P* < 0.05 will be considered statistically significant for all analyses.

For rs-fMRI and DTI data, a two-way mixed design ANOVA will be performed, with between-subject factor “Group” and within-subject factor “Time” on the data generated in the data processing step, including Eg, El, network betweenness, clustering coefficient, and FA AI. For tb-fMRI data, a whole brain paired T-test will be performed between the task state blocks and baseline blocks in the FC group, and the voxels whose t value is higher than the threshold will be regarded as the activated brain region. For cM1-LF, cPMd-HF, and CON groups, a two-way mixed design ANOVA, with between-subject factor “Group” and within-subject factor “Time” will be performed within the former activated brain region. The most significant point of “Group” × “Time” effect in the activated brain region will be used as the center to construct spherical balls with a radius of 6 mm, and the spherical balls will be regarded as the ROIs. Finally, to obtain the effective connectivity of each patient at different time points, the average time series of all voxels in each ROI will be subjected to dynamic causal model (DCM) analysis.

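### Time since onset ranges from 3 to 12 months but is not in the stated Group × Time model; adding it as a covariate would buy a modest gain in precision

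*Protocol article*

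**What the plan says.** Eligibility (Table 1) sets the window at "3–12 months since stroke onset". The Study design section describes the population as "chronic (onset time > 3 months) subcortical stroke patients with severe hemiplegia". The Background states in general terms that stroke patients can improve on their own, but gives no rate and no time course.

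Under Randomization and grouping, patients are "randomly assigned to three groups with 20 patients in each group", and the sequence comes from a list produced in Stata by a third-party statistician. No stratification or minimisation factor is described. One of the three arms is a "sham-stimulation control (CON) group".

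Under Group-level analysis, "a two-way mixed design ANOVA with between-subject factor “Group” and within-subject factor “Time” will be performed for the clinical and electrophysiological changes". No covariate is named. The same section plans a one-way ANOVA of demographic characteristics and T0 values across groups. Time since onset is not mentioned there, and it appears in the article only as an eligibility limit.

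**The concern.** Time since onset has to be known for every patient before Table 1 can be applied, and it is a natural candidate to predict how much a patient changes over follow-up, which runs about 7 weeks (3 weeks of treatment plus 4 weeks). If patients nearer the 3-month end change more than those nearer 12 months, two things follow in a trial of this size. The arms will often differ somewhat in time since onset by chance, and the spread in change that it causes is counted as unexplained error in the Group × Time test. A baseline test across arms can show an imbalance but does nothing to remove it.

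What is at stake is precision and ease of interpretation. Only a different amount of change matters, because the Group × Time comparison already removes stable differences in level between patients.

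**Working it through.** **Inputs.** From the article: window 3–12 months; 20 per arm; dropout 30%; FM-UL rising from 30 to 43, a difference of 13; SD 17; power 80%; significance level 0.05. Assumed, because the article does not give them: uniform entry over the window, the extra gain of earlier patients, and the share R² of variance in the compared quantity that time since onset explains.

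**The plan's own figure.** A one-sample before–after calculation gives n = (17 × (1.960 + 0.842) / 13)² = 13.4, rounded up to 14. Then 14 / (1 − 0.30) = 20 per arm and 60 in total, as stated. So 14 completers per arm is the figure to carry forward. For a comparison between two arms with the same 13 and 17, power is Φ(13 / (17 × √(2/14)) − 1.96) = Φ(2.023 − 1.960) = 52.5%. That the plan's figure reproduces only as a within-group change is a separate matter; here 52.5% serves as the unadjusted starting point.

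**How large is chance imbalance?** The SD of a uniform distribution on 3–12 is 9/√12 = 2.60 months. The SE of the difference in means between two arms is:

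- 20 per arm: 2.60 × √(2/20) = 0.82 months, 95% range about ±1.6
- 14 per arm: 2.60 × √(2/14) = 0.98 months, 95% range about ±1.9

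By simulation, the largest gap among the three arms exceeds 1 month in about 45% of trials with 20 per arm and 57% with 14.

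**What would that do to the estimate?** Purely for illustration, let one third of patients (those at 3–6 months under uniform entry) gain an extra g FM-UL points over follow-up. The 95% chance shift between two arms of 14 is 1.96 × g × √(2 × ⅓ × ⅔ / 14), and the added variance is g² × ⅓ × ⅔.

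| g (points) | 95% chance shift | Added variance | Share of 17² = 289 |
|---|---|---|---|
| 1 | ±0.35 | 0.22 | 0.1% |
| 2 | ±0.70 | 0.89 | 0.3% |
| 3 | ±1.05 | 2.00 | 0.7% |
| 5 | ±1.75 | 5.56 | 1.9% |

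The planned difference is 13. If the SD of change were 7.6 (17 × √(2 × 0.1), assuming a correlation of 0.9 between visits), the shares would be 0.4% to 9.6%.

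**What does adjustment gain?** Replace 17 by 17 × √(1 − R²):

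| R² (assumed) | Residual SD | Power, 14 per arm | Completers per arm for 80% |
|---|---|---|---|
| 0 | 17.0 | 52.5% | 27 |
| 2% | 16.8 | 53.3% | 27 |
| 5% | 16.6 | 54.6% | 26 |
| 10% | 16.1 | 56.9% | 25 |
| 20% | 15.2 | 61.9% | 22 |

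Confidence intervals shrink by the factor √(1 − R²): about 1% at R² = 2% and 11% at R² = 20%. In the illustration, with SD 17, an R² of 2% needs g = √(0.02 × 289 / 0.222) ≈ 5 points and 20% needs about 16 points, which is more than the whole planned difference. The upper rows are therefore generous unless the SD of change is well below 17.

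**The case against.** The strongest objection is that this is a journal article, and such articles often leave stratification factors and covariates to the full protocol or analysis plan. For randomisation that stands: the most one can say is that no balancing is described. For the analysis it stands only in part. The article commits to a specific model with two named factors, so adding a covariate changes a stated analysis and is more than filling in missing detail.

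A second objection is that randomisation with a concurrent sham arm, and the same conventional rehabilitation in all arms, already deals with natural recovery. This stands. A reader might infer that an arm with more early patients would yield a biased treatment effect. The design does not support that: the imbalance is random error, and the 5% significance level already allows for it.

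A third objection is that the effect is small. This also largely stands: with SD 17 and extra gains of 1 to 5 points, time since onset accounts for under 2% of the variance. The point survives because the remedy is nearly free.

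**Conclusion.** The point holds as a minor one about precision. Patients across a nine-month window are analysed together with no term for time since onset, and a gap of a month or more between some pair of arms is likely in roughly half of such trials under uniform entry. Adjusting would raise two-sample power at 14 completers per arm from 52.5% to 53–62% for an assumed R² of 2–20%. The article supplies neither the R² nor the distribution of entry times, so these are ranges and not predictions.

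Two stronger readings are tempting and not supported:

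- **The definition of chronic is inconsistent, or the pooled result fails to answer the chronic-stroke question.** The Study design section sets the lower bound at more than 3 months, and Table 1 gives the full window with its upper limit. The summary sentence merely omits that limit. The Background does say that "there is no clear recommendation for rTMS stimulation parameters in patients with chronic stroke", and it ties the existing guidance to the sub-acute phase, but by the article's own definition the enrolled patients are chronic. Where that phase should begin is a clinical question of generalisability.
- **Patients beyond 6 months need a separate contrast, or allocation should now be stratified.** No 6-month boundary or recovery plateau appears in the article. Under uniform entry, two thirds of 14 completers leaves about 9 per arm, too few for a useful comparison. Changing the allocation scheme after recruitment has begun is a debatable trade-off that so small a gain does not justify.

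**What to change.** In the Group-level analysis, pre-specify time since onset at T0, as a continuous variable, as a covariate for the clinical and electrophysiological outcomes, together with its interaction with Time. The interaction is essential: a value that is constant within a patient cannot touch the Group × Time comparison through its main effect alone. Settle this before the groups are compared, and tabulate time since onset by arm with the other baseline characteristics.

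The cost is small. The value is already obtained at screening. With three visits, the main effect uses one degree of freedom and the interaction two. With 42 completers, the between-patient error degrees of freedom go from 39 to 38 and the within-patient ones from 78 to 76. Eligibility, allocation and sample size need no change.

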### Randomization and grouping

The 60 eligible stroke patients will be randomly assigned to three groups with 20 patients in each group: low-frequency rTMS of cM1 (cM1-LF) group, high-frequency rTMS of cPMd (cPMd-HF) group, and sham-stimulation control (CON) group. The random sequence will be created using STATA 12.0 software (StataCorp, Texas, USA) by a professional third-party statistician from Fudan University. The randomization list will only be known by this research coordinator and will be concealed from other study personnel. However, the research coordinator will not participate in recruitment, subsequent intervention and assessment, and final data analysis. In addition, 20 healthy people will be recruited into the healthy control (HC) group. The HC group will be matched with stroke groups in terms of age, gender, and education.

### Blinding

This trial will utilize a randomized, patient-and assessor-blinded, parallel-group design. The patients, assessors, and statisticians will not be aware of the group assignment. They will only be informed of the group’s identification (group A, group B, and group C) but not be aware of which group is the cM1-LF, cPMd-HF, and CON group. Physicians will be divided into two groups: one group responsible for screening and assessing patients, and the other group responsible for applying rTMS intervention. Notably, the former will be blinded to group assignment, but the later cannot be blinded since applying rTMS over different stimulation sites implies the assignment.

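### Patients and assessors are given a shared group letter, so recognising the treatment of one high-frequency patient would unmask that whole arm to an assessor

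*Protocol article*

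**What the plan says.** The Blinding section of the protocol article first states that "The patients, assessors, and statisticians will not be aware of the group assignment". The next sentence, about the same three parties, says they are told the group's "identification (group A, group B, and group C) but not be aware of which group is the cM1-LF, cPMd-HF, and CON group". The letter is therefore disclosed and its meaning withheld.

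The same section divides the physicians into "one group responsible for screening and assessing patients, and the other group responsible for applying rTMS intervention". It calls the screening and assessing group blinded and says the rTMS group cannot be.

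Under Randomization and grouping, "The 60 eligible stroke patients will be randomly assigned to three groups with 20 patients in each group". The list is known only to a coordinator who takes no part in recruitment, intervention, assessment or analysis, and it "will be concealed from other study personnel".

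The intervention section gives cPMd-HF a different pulse pattern from cM1-LF. The sham arm uses the cM1-LF parameters and reproduces the cM1-LF sound.

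**The concern.** A letter shared by a whole arm masks the treatment's name but not membership of the arm. Two things follow.

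- **A leak spreads.** Once an assessor links one patient's letter to a treatment, every patient with that letter is unmasked.
- **Expectations form without a leak.** A rater who sees letters can come to believe that one letter does better and carry that belief into later ratings.

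The clinical outcomes include FM-UL, ARAT, WMFT, MMT and MAS, all scored by an assessor, so the risk is detection bias in the comparison between arms. The arm easiest to recognise, cPMd-HF, is also the one that Aims and hypotheses expects to be best, so any bias could favour the study hypothesis.

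A secondary question is whether physicians who both assess and screen could use the letters of enrolled patients to anticipate later assignments.

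**Working it through.** The protocol gives no figure on this point to reproduce. The check is a comparison of passages followed by counting.

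**1. Which arms can be told apart by their rhythm (intervention section)**
- cM1-LF: 10 pulses at 1 Hz = 10 s, then 2 s of silence; 100 × 12 s = 1200 s = 20 min.
- cPMd-HF: 50 pulses at 5 Hz = 10 s, then 50 s of silence; 20 × 60 s = 1200 s = 20 min.
- Sham: same pattern and sound as cM1-LF.

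The durations match but the rhythm does not. Sound and rhythm can identify cPMd-HF. They cannot separate cM1-LF from sham.

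**2. Effect of one decoded cPMd-HF patient (20 per arm, 60 in total)**

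This assumes that the assessor holds every patient's letter.
- Shared letters: 20/60 = 33% unmasked. The other 40 are known to be cM1-LF or sham.
- Individual codes: 1/60 = 1.7% unmasked.
- Expected correct arm guesses by the assessor: with shared letters, 20 + 40 × 1/2 = 40 of 60 (67%); with individual codes, 1 + 59 × 20/59 = 21 of 60 (35%); with no leak, 20 of 60 (33%).
- A second decoded letter would fix the third and unmask all 60. By step 1, that needs a source other than the sound, for example the unblinded rTMS physicians.

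**3. Predictability of later letters**

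This applies only if screeners see the letters during recruitment. An assignment is certain in advance when all remaining places carry one letter. For a sequence of length B with B/3 per letter, the expected number of certain assignments is B / (2B/3 + 1).
- 20:20:20 fixed and nothing else, B = 60: 60/41 = 1.46. A simulation of 5000 sequences gave 1.47. The same simulation put correct guesses of the next letter at 42%, against 33% by chance.
- The article states no block size. If blocks were used, with a fixed size known to the screener, the range would be:

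| Assumed block | Certain in advance, of 60 | Simulated correct guesses |
|---|---|---|
| 12 | 5 × 12/9 = 6.7 | 51% |
| 6 | 10 × 6/5 = 12 | 56% |
| 3 | 20 × 3/3 = 20 | 61% |

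What is predicted is a letter. It becomes a treatment only if that letter has been decoded.

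**The case against.** The sentence on letters covers three parties at once and does not say who receives which label or when. It could mean only that, wherever groups appear, they appear as A, B and C, which is ordinary practice for a statistician. An article condenses such detail. A patient would presumably learn only his or her own letter. Assessors are a separate group from those giving rTMS, and nothing places them at treatment sessions. No leak is documented, so 20 of 60 is the consequence of an event whose probability is unknown.

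Most of this limits the finding without removing it. The rule names patients and assessors explicitly, and its natural reading gives them a letter; if something narrower is meant, the sentence needs rewording anyway. Assessors need not attend sessions, because patients can describe them. The conditional nature of the 20 of 60 stands.

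Two stronger readings are tempting, and the document does not support them.

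- **That screening physicians see the running allocation, so that concealment fails.** A reader might infer this from the combined screening and assessing role. But the Blinding section calls that group blinded, the list is held by a coordinator outside recruitment, and nothing says when letters are released or that anyone keeps a cumulative log. Study design also names two recruiting hospitals (the eligibility section names one), so no single screener need see every letter. Blocks are not mentioned, and the last place in a block is certain only if its size is fixed and known.
- **That audible differences would unmask all 60 patients.** Sham is matched to the cM1-LF sound, so this cue stops at cPMd-HF.

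**Conclusion.** The point holds for the masking of patients and assessors and should be corrected. As written, the plan discloses a label common to 20 patients. Decoding the cPMd-HF letter once would unmask a third of the trial and halve the uncertainty about the rest, against 1 of 60 with individual codes. This assumes that assessors hold the letters of the patients they rate, as the Blinding section implies, and that one patient's treatment becomes recognisable to them. Neither the chance of a leak nor the resulting bias in FM-UL can be estimated from the document. The risk of arm-level expectations needs no leak.

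The allocation question is conditional and minor: about 1.5 of 60 letters certain in advance under the only stated constraint, and only for someone who sees every earlier letter. It does not show that concealment is broken or that selection at enrolment would occur. A/B/C coding for the statistician is sound.

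**What to change.** Replace the sentence on group letters in the Blinding section with three rules:

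1. Patients are identified to themselves, to assessors and to screeners only by a unique patient number; no group letter appears on any form these parties see, at any time.
2. The coordinator releases the arm only to the treating physicians, one patient at a time, after enrolment is complete.
3. Labels A, B and C go only to the analysing statistician, after database lock.

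This does not stop a patient from describing the sessions. It confines what is revealed to that patient. It also removes the conditional allocation question, because screeners would then hold no sequence of letters.

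The cost is one paragraph and a change to case report form labelling; no staff, visits or treatments change. Trial status reports recruitment as incomplete at submission, so the change could still protect later assessments. Letters already disclosed cannot be withdrawn, and the trial report should say which assessments were made under the old labelling.
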